Therefore, this study offers patients with breast cancer the choice of replacing the initial face-to-face consultation prior to DNA-testing (usual care DNA-intake procedure) by a home information package including telephone, written and digital information consisting of a website and educational movie (DNA-direct procedure). DNA-testing will thus be performed prior to genetic counseling, contrary to current practice. At the first face-to-face contact, counselors will be able to disclose DNA-results and customized advice to patients. This eliminates extraneous information which is not applicable to the individual patient, and provides patients with the information they desire in a quick and patient-centric manner.

The aim of this intervention study is to compare this new DNA-direct procedure to current practice (DNA-intake procedure). The effects of the DNA-direct procedure on the experience and psychosocial distress on patients with breast cancer, as well as the speed and quality of genetic advice, will be evaluated. The hypothesis is that undergoing the DNA-direct procedure does not lead to increased levels of psychosocial distress as compared to the usual care DNA-intake procedure, with equal levels of patient satisfaction plus shorter waiting and processing times. A trend similar to traditional *BRCA1/2* testing – a short term increase in distress, falling back to pre-testing levels over time [33-39] – is expected in the DNA-direct procedure. This would make DNA-direct an acceptable procedure for patients with breast cancer undergoing genetic testing, with the goal of more customized care, and a shorter period of uncertainty. Moreover, it would facilitate taking genetic advice into account for the treatment and follow-up of breast cancer.

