### Sample size calculation

For this intervention study, participants are not randomized into groups, but given their own choice. This leads to certain complications when it comes to a formal power calculation. First, the ratio between the two procedures is unknown: this may either be balanced (50% versus 50%) or unbalanced (e.g. 20% versus 80%). Second, due to not randomizing, the results will have to be corrected for multiple confounders, which are not all known at this point. The sample size, based on aforementioned ratio between both groups (choice of procedure), needs to be large enough to be able to integrate these confounders into a regression model. Using a power of 80% and a two-tailed probability level for statistical significance testing of 0.05, while taking into account group ratios ranging from balanced (50% versus 50%) versus unbalanced (to an estimated maximum of 20% versus 80%), the total sample size has been set to 150 patients with breast cancer.

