### Statistical analysis

To compare general characteristics, baseline and follow-up results between the intervention versus control group, the unpaired *t*-test will be used for continuous variables, Mann–Whitney *U* test for non-parametric variables and chi-square test for dichotomous variables. For the comparison of baseline versus follow-up results within each group, the paired *t*-test will be used for continuous, Wilcoxon test for non-parametric and McNemar’s test for dichotomous variables. Multivariate analysis will consist of a regression model using the follow-up results as outcome (dependent) variables, to be compared between the intervention versus control groups as independent variables, with the baseline results as covariates supplemented by variables that were found to be statistically significant in previous univariate analyses. The probability level for statistical significance testing is set at 0.05 (two-tailed). The SPSS 18.0 statistical package will be used to analyze the data.

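### The hypothesis of no increase in distress and equal satisfaction is paired only with two-tailed difference tests and no margin, so the plan defines no result that could support it

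*Protocol article*

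**What the plan says.** The last paragraph of the Background states the hypothesis: DNA-direct "does not lead to increased levels of psychosocial distress as compared to the usual care DNA-intake procedure, with equal levels of patient satisfaction", together with shorter waiting and processing times. It then draws the consequence: "This would make DNA-direct an acceptable procedure for patients with breast cancer undergoing genetic testing". The Abstract names satisfaction and psychological distress as the primary outcome measures, and the Discussion repeats acceptability as the aim.

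The Sample size calculation rests on testing for a difference: "Using a power of 80% and a two-tailed probability level for statistical significance testing of 0.05". It allows for group ratios from 50:50 to an estimated maximum of 20:80, and concludes that "the total sample size has been set to 150 patients with breast cancer". It gives no effect size, SD or margin.

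The Statistical analysis section begins "To compare general characteristics, baseline and follow-up results between the intervention versus control group, the unpaired" *t*-test, and adds Mann–Whitney and chi-square tests, with paired counterparts within groups. It continues: "Multivariate analysis will consist of a regression model using the follow-up results as outcome (dependent) variables", with group as independent variable and baseline results as covariates. The error level is again 0.05, two-tailed. No equivalence or non-inferiority test, margin or confidence-interval criterion appears anywhere in the article. The thresholds given for the GHQ-12, the IES and the Decisional Conflict Scale classify individual scores. They are not limits for a difference between groups.

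**The concern.** No increase in distress is a non-inferiority claim, and equal satisfaction is an equivalence claim. The planned tests take no difference as the null hypothesis. A significant result against DNA-direct would refute the claim. If the two procedures are in truth alike, the expected result is non-significance, and that does not show the absence of an increase. It also becomes more likely as the study gets smaller or noisier.

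The stakes are considerable. The Background explains that counselling before testing was adopted because of concern about psychological consequences, and DNA-direct removes the face-to-face part of it. Whether a relevant rise in distress can be ruled out is a central question, and the plan sets no criterion for answering it.

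**Working it through.** **Inputs from the protocol article:** N = 150, ratio 50:50 to 20:80 (75/75 to 30/120), two-tailed α = 0.05, power 80%. **Assumptions, because the article gives none:** true increases and margins in SD units, a baseline-to-follow-up correlation of r = 0.5, and no dropout.

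**Step 1. The plan's own figure.** N = 150 cannot be reproduced without an effect size. It can be solved backwards. In SD units, SE = √(1/n₁ + 1/n₂):
- 75/75: √(2/75) = 0.1633
- 30/120: √(1/30 + 1/120) = 0.2041

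The difference detectable with 80% power is (1.960 + 0.842) × SE, which is 0.46 SD (75/75) and 0.57 SD (30/120).

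**Step 2. What a non-significant result would leave open.** The 95% CI half-width is 1.96 × SE, which is 0.32 SD and 0.40 SD. Even an observed difference of exactly zero leaves increases up to those values inside the interval.

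**Step 3. Probability of p > 0.05 when distress truly rises by δ.** This uses the non-central t distribution with non-centrality δ/SE. Without adjustment there are 148 degrees of freedom. With baseline adjustment at r = 0.5, SE is multiplied by √(1 − 0.25) = 0.866, giving 0.1414 and 0.1768, with 147 degrees of freedom.

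| True increase | Analysis | 75/75: δ/SE | P(non-significant) | 30/120: δ/SE | P(non-significant) |
|---|---|---|---|---|---|
| 0.3 SD | unadjusted | 1.84 | 55% | 1.47 | 69% |
| 0.3 SD | r = 0.5 | 2.12 | 44% | 1.70 | 61% |
| 0.4 SD | unadjusted | 2.45 | 32% | 1.96 | 51% |
| 0.4 SD | r = 0.5 | 2.83 | 20% | 2.26 | 39% |

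A normal approximation agrees to within one percentage point.

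**Step 4. What N = 150 would support with a margin.** Take a true difference of zero and ask for the unfavourable limit of the two-sided 95% CI to exclude a margin M. The power depends on M/SE:
- M = 0.4 SD, unadjusted: 68% (75/75) and about 50% (30/120)
- M = 0.5 SD, unadjusted: 86% and 68%
- M = 0.5 SD, r = 0.5: 94% and 80%

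The last line can apply only to distress. The satisfaction measures stand under the heading for experiences at follow-up and have no baseline score, so for them the unadjusted figures apply. If both claims must succeed and are taken as independent (a further assumption), joint power at 0.5 SD is 0.940 × 0.860 = 81% at 75/75 and 0.802 × 0.682 = 55% at 30/120.

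**The case against.** The strongest reply is that the article nowhere says a non-significant result will be read as acceptability. That is correct. A reader might infer such a rule from the Background and the Statistical analysis section taken together, but it is not written, and a rule for interpretation could stand in a fuller document that is not shown. What remains is a mismatch between elements the article itself fixes: hypothesis, tests, error level and basis for the sample size.

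A reader might also infer that the whole conclusion on acceptability rests on absence of evidence. The article does not support this. Choice of procedure is a primary outcome in its own right. Participants are asked whether they would choose DNA-direct again or advise it, and interviews are planned. Shorter waiting and processing times is a superiority claim that difference tests suit. Only the distress and satisfaction parts are affected.

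Nor is imbalance a fact. The ratio is called unknown, with 20:80 as the estimated maximum. The mismatch exists at 50:50 too and is worse at 20:80.

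Unadjusted figures alone would overstate the problem, since a regression with baseline as covariate is already planned. The adjusted rows in the table allow for that, and the probabilities remain material.

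Finally, a significant reduction in distress would of course also show no increase. But the hypothesis does not predict one, and significantly higher satisfaction would not be equal satisfaction.

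**Conclusion.** The point holds for two parts of the hypothesis, distress and satisfaction. As written, the planned tests can contradict these parts. They cannot support them if the procedures perform alike. The size depends on assumed effects: for a true rise of 0.3 to 0.4 SD, the probability of a non-significant result runs from 20% (0.4 SD, 75/75, r = 0.5) to 69% (0.3 SD, 30/120, unadjusted).

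The article does not say what increase would matter clinically, so these values are illustrations. They do not show that 0.3 or 0.4 SD is relevant, and the margins of 0.4 and 0.5 SD used above are not recommendations. Dropout and adjustment for confounders would reduce precision further and are not counted.

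**What to change.** In Statistical analysis:

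1. Name one lead distress score and one lead satisfaction score. Several measures are listed under Primary outcomes and none is singled out.
2. Before the data are analysed, fix a margin for each on clinical grounds.
3. Report the adjusted difference, DNA-direct minus DNA-intake, with its two-sided 95% CI.
4. Claim that distress is not increased, or that satisfaction is not worse, only if the unfavourable limit excludes the margin. Claim equal satisfaction only if both limits lie within the margin. Otherwise report the result as inconclusive.

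In Sample size calculation, state what 150 patients support at 50:50 and 20:80 for the chosen margins, and credit any gain from baseline adjustment to distress only. Leave the difference tests for waiting and processing times as they are.

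The cost is a decision on the margins and changes of wording. No patients, visits or data are added. The downside is that the result may have to be called inconclusive, most likely if the groups are unbalanced. A margin deals with sampling error only and does not remove confounding by the patients' own choice of procedure.

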## Methods/design

### Design

The study examines the effect of the DNA-direct procedure on the experience and psychological distress of patients with breast cancer as well as several secondary outcome measures, including waiting and processing times, as compared to the current DNA-intake procedure. Two groups will be compared: the intervention group, who choose to undergo the DNA-direct procedure, and the control group, who will receive care as usual (DNA-intake procedure). Participants may choose freely between the DNA-direct versus DNA-intake procedures. This study is not randomized due to the wish to evaluate whether there is indeed a desire for the proposed DNA-direct procedure amongst patients with breast cancer, and to evaluate the reasons stated for preferring one procedure over the other.

### Ethical consideration

The study has been approved by the medical ethical committee of the Radboud University Nijmegen Medical Centre. Full medical ethical approval has been obtained in July 2011.

### Study sample

All female patients previously or currently diagnosed with breast cancer and referred to the department of Clinical Genetics of the Radboud University Nijmegen Medical Centre from August 9th 2011 are eligible for inclusion. Recruitment will continue until the desired total of 150 participants is reached. Patients who have problems reading Dutch text, problems with family communication or problems of psychological/psychiatric nature (including current use of related medication) will be excluded.

### Recruitment

Patients are sent a written letter by a trained doctor announcing a phone call, in which the two choices of procedure are explained (DNA-intake for a face-to-face intake consultation prior to DNA-testing, versus DNA-direct for a home package of telephone, written and digital information) and exclusion criteria are checked. The aim of this telephone approach is triage: by checking for exclusion criteria such as psychological problems, patients who aren’t deemed suitable for DNA-direct (due to its dependency on the patient’s own decision making ability) are filtered out and instead invited for a regular intake consultation, where further psychosocial support is immediately available prior to DNA-testing. Genetic counseling is not offered by phone: questions of this nature are deferred to the personal consultations. The triage phone call has been thoroughly practiced (over 20 times) by the involved doctor with people both specialized and not specialized in clinical genetics.

All patients receive the same two questionnaires, one at inclusion (baseline) and one after completion of the chosen genetic counseling procedure (follow-up). Patients who are confirmed carriers of a *BRCA1/2* mutation, patients reporting problems with the chosen procedure, and randomly selected (n = 10) patients will be invited for a 30 min semi-structured telephone interview.

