### Intervention

Patients who choose the DNA-direct procedure, receive a home informational package including an informational letter, a link to a website including a short educational movie about hereditary breast cancer and DNA-testing. Also included are two EDTA blood vials with informed consent and family history forms. Patients are instructed to call their family doctor assistant to ask where to have their blood drawn, then return the vials plus signed forms in the appropriate return package. An appointment for a personal consultation to disclose results is set 8 weeks after DNA-testing has commenced.

All patients (whether they choose DNA-direct or DNA-intake) are seen by one of five selected genetic counselors, each of whom has extensive experience in genetic counseling for hereditary cancer. These counselors have had multiple meetings in order to structure the DNA-direct consultations as follows: If no mutation is found, further screening advice is formulated based on familial risk scores: FHAT [43], Myriad [44] and Claus/van Asperen [45,46]. Further evaluation of family history and features of other hereditary cancer syndromes may be required. In the case of a pathogenic *BRCA1* or *BRCA2* mutation, this result is disclosed immediately, first allowing the patient to react, followed by an explanation of the consequences, including prevention measures and family evaluation. If considered necessary, a second consultation is offered for further genetic counseling. All confirmed *BRCA1/2* carriers will be approached by a social worker to extend psychosocial support if needed, as in usual care.

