### Study outcomes

Participants are asked to fill out a questionnaire twice: at baseline and following the conclusion of genetic counseling and/or testing (follow-up). Some measures are used in both questionnaires, while others are only included in either baseline or follow-up.

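### In a self-selected comparison, breast cancer treatment phase enters the distress model only if it passes a univariate significance filter, although follow-up timing varies with the procedure

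*Protocol article*

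**What the plan says.** All references are to the protocol article.

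- **Allocation.** Under Design, participants choose freely between DNA-direct and DNA-intake; there is no randomization.
- **Who enters.** Study sample: "All female patients previously or currently diagnosed with breast cancer" who are referred to the department are eligible.
- **When follow-up is taken.** Recruitment: "All patients receive the same two questionnaires, one at inclusion (baseline) and one after completion of the chosen genetic counseling procedure (follow-up"). Study outcomes gives the same anchor: "at baseline and following the conclusion of genetic counseling and/or testing (follow-up"). Neither section gives a fixed interval from baseline.
- **Expected length.** The Background describes "the choice of replacing the initial face-to-face consultation prior to DNA-testing (usual care DNA-intake procedure) by a home information package" and hypothesizes no increase in distress, "with equal levels of patient satisfaction plus shorter waiting and processing times". Intervention adds, for DNA-direct: "An appointment for a personal consultation to disclose results is set 8 weeks after DNA-testing has commenced". No total duration is given for either procedure.
- **Adjustment.** Statistical analysis regresses follow-up results on group, "with the baseline results as covariates supplemented by variables" that were significant in the preceding univariate analyses, at the two-sided 0.05 level.
- **Data available.** Cancer status is collected at baseline (Demographical and breast cancer information). Waiting and processing times are gathered (Other measures).

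**The concern.** Three of the psychological-burden measures are not specific to genetic testing: the two global quality-of-life items, the GHQ-12 and the Cancer Worry Scale, which measures fear of recurrence. All three can move as a woman goes through and recovers from breast cancer treatment, whichever counseling procedure she chose.

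Treatment phase can bias the comparison in two ways. Women under treatment may prefer one procedure. The Background notes that recently diagnosed women may want their BRCA1/2 status for surgical decisions, which makes this plausible. Also, if the procedures take different times, the groups are measured after different amounts of recovery.

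Adjusting for the baseline score does not settle this. Two women with equal baseline scores, one in treatment and one long past it, can be on different trajectories.

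The hypothesis is that DNA-direct does not raise distress, so bias in either direction matters. It could make an acceptable procedure look worse, or hide a real increase.

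**Working it through.** **1. The stated sample size.** Sample size calculation gives 150 in total, 80% power, two-sided 0.05, and splits from 50:50 to 20:80. It states no effect size, SD or margin, so 150 cannot be reproduced. It can be inverted:

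d = (z₀.₉₇₅ + z₀.₈₀) × √(1/n₁ + 1/n₂) = (1.960 + 0.842) × √(1/n₁ + 1/n₂)

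- 75:75: 2.802 × 0.1633 = 0.457 SD
- 30:120: 2.802 × 0.2041 = 0.572 SD

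**2. What this means for the filter.** The same formula governs an unpaired comparison of a continuous covariate, such as time since diagnosis, between the groups. For a true imbalance δ (in SD), the chance that the covariate reaches p < 0.05 is about

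1 − Φ(1.96 − δ/s) + Φ(−1.96 − δ/s), with s = √(1/n₁ + 1/n₂).

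| True imbalance (assumed) | Kept at 75:75 | Kept at 30:120 |
|---|---|---|
| 0.2 SD | 23.2% | 16.5% |
| 0.3 SD | 45.1% | 31.2% |

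An imbalance of 0.3 SD would thus be left out of the model more often than not at either split. Treatment phase in two categories would be compared by chi-square test. The low power carries over, although the SD scale then holds only approximately.

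**3. Could the effect on distress matter?** The article gives neither the gap in duration nor a recovery rate, so this is illustration only. Assume no procedure effect and linear recovery, and take bias = rate × gap. The chance of a falsely significant group difference comes from the formula in step 2, with the bias in place of δ.

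| Assumed rate | Assumed gap | Bias | 75:75 | 30:120 |
|---|---|---|---|---|
| 0.05 SD/month | 1 month | 0.05 SD | 6.1% | 5.7% |
| 0.1 SD/month | 2 months | 0.2 SD | 23.2% | 16.5% |
| 0.2 SD/month | 3 months | 0.6 SD | 95.7% | 83.6% |

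The nominal rate is 5%. The range runs from negligible to larger than the detectable difference in step 1. The table shows that the question is open; it does not estimate the bias.

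**4. Direction.** If distress is falling, the group measured sooner looks worse; if it is rising, that group looks better. Which group is measured sooner is not fixed either. The hypothesis expects DNA-direct to be faster. But the Discussion says that DNA-intake patients who do not meet the testing criteria are not offered a test, whereas such patients can be tested under DNA-direct. For those women DNA-intake may end first.

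**The case against.** **Follow-up at completion is a sound choice.** It puts both groups at the same counseling milestone. At a fixed calendar time, one group could be past disclosure and the other still waiting. The rise and fall in distress that the Background expects is tied to testing, which also favors aligning on completion. This stands, and the timing should not be changed.

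**The covariate list may be settled elsewhere.** The article says that results will be corrected for confounders not all known yet, and an analysis plan may name them. Cancer status is collected, so it is already a candidate. This stands in part: the model is not limited to baseline scores. But the article itself states the rule for adding covariates, and that rule is the weakness.

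**Stronger readings that a reader might infer.**

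- *DNA-direct women are always measured sooner, so the bias is known.* Shorter times are a hypothesis, and untested DNA-intake women may finish early.
- *The groups differ in treatment phase.* The article shows a mixed sample and free choice, which make this possible. It does not say that recently diagnosed women will prefer DNA-direct.
- *The artefact can be stated in Impact of Event Scale points.* Under Cancer specific distress, the follow-up scale asks only about genetic predisposition; the breast cancer version is baseline only. A breast cancer recovery rate does not transfer to it.
- *A difference belongs to the procedure only if it survives adjustment for elapsed time.* Duration is part of what DNA-direct changes, so such adjustment would remove some of the intervention's own effect. Time from diagnosis to follow-up has the same problem, because it adds a confounder (time before baseline) to a consequence of the procedure (time after it).

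**Conclusion.** The point holds as a weakness in the covariate rule. In a non-randomized comparison with mixed disease timing, treatment phase is a plausible confounder known in advance, yet the stated model lets it in only through a significance test. At N = 150 that test reaches 80% power only at about 0.46 SD (75:75) or 0.57 SD (30:120), so a real confounder can drop out.

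This rests on two assumptions: that treatment phase is related to quality of life, GHQ-12 or cancer worry beyond the baseline score, and that it may differ between the chosen groups. The article makes both plausible and proves neither. The size and direction of any bias are undetermined. Follow-up at completion is not itself an error.

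**What to change.** 1. In the regression for the psychological-burden outcomes, always include baseline cancer status or treatment phase, whatever its univariate p-value. Add time from diagnosis to baseline on the same terms if the date is available. The article lists cancer status but not a diagnosis date, so this should be confirmed.
2. Report the baseline-to-follow-up interval by group, using the waiting and processing times already gathered.
3. Show a model that also includes this interval, as a sensitivity analysis only, and say that the interval is partly a consequence of the procedure.
4. Keep follow-up at completion.

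The cost is one or two degrees of freedom and slightly less precision, felt most if one group is as small as 30. No extra patients, visits or questionnaires are needed. If the diagnosis date is not recorded, adding it means one more data item.
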